#### Effectiveness outcomes

The *primary outcome* is timely HPV vaccine initiation and completion (2 doses) rates of 11-12 year olds. We define completion as a second valid dose 6–12 months after their first dose. *Secondary outcomes* include timely initiation and completion (2 or 3 doses) for adolescent patients 13-17 years old (catch-up). For 13-14 year olds, we define completion as valid dose 6–12 months after their first dose. For 15–17 year olds, we define completion as a second valid dose 1-2 months after their first dose and a third valid dose 6 months after their first dose. Our outcome data will be single measurements taken from individual patients, but we will randomly select patient EHR data for each data pull [87]. These patient data will also include demographic data (race/ethnicity, gender, and age), which we will use to facilitate statistical analyses where potential confounding by these variables should be controlled.

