### Setting and randomization

Our three FQHC collaborators are Community Health Network (CHN), Project Vida Health Center (PVHC), and Spring Branch Community Health Center (SBCHC), which service different areas of Texas. We recruited these FQHCs in collaboration with through the Texas Association of Community Health Centers (TACHC). The Director of Clinical Affairs emailed their members a description of the study, the inclusion criteria below, and the PI’s email to contact directly if interested in participating. *Inclusion Criteria*. FQHCs were eligible for the trial if they met the following criteria: (1) have less than 60% HPV vaccine initiation rate for 11–12 year old adolescents overall at their practice sites (primary outcome); (2) have family medicine and/or pediatric practices; and (3) have a total adolescent patient population at least 50% Latino/a. *Exclusion Criteria*. FQHCs were excluded if they participated in the pilot study. *Randomization*. Our biostatistician will randomly assign a FQHC out of the three participating to begin using a simple random sorting. Once randomized, the FQHC will stay in their assigned position all five years.

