### Data collection

Our approach uses a stepped-wedge, cluster randomized control design to test the strategies used by the practice [87]. We will randomize three FQHC’s with three practices each (*n* = 9 practices), who meet eligibility criteria requirements, to begin the intervention first, second, or third. All practices within a given FQHC are in the same cluster. The design involves random and sequential crossover of an FQHC’s 3 practices from the control period to implementation of the facilitator-driven strategies until all are exposed [87]. We will assess primary and secondary effectiveness outcomes at baseline and every three months afterward. We powered the trial based on the primary outcome of HPV vaccine initiation and completion of 11–12 year olds.

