### Analyses

#### Sample size justification

Based on the 2019-2021 data from three participating FQHCs, the average number of 11-12 year old patients seen per practice is 109 per 3 months, the HPV initiation rate ranges from 24.6% to 40.9% with an ICC of 0.026, and the HPV completion rate ranges from < 1% to 14.7% with an ICC of 0.003. Conservatively, we assume there will be an average of 30, 11–12 year old patients per practice per 3 months. We assume the average HPV initiation rate during the control period varies from 20 to 60% with an ICC of 0.026, and the average HPV completion rate during the control period varies from 3% to 40% with an ICC of 0.003.

A sample of 9 practices (three practices per FQHC) in a custom stepped-wedge design (see Table 3, 0 means control period, “.” means implementation/transition period, and 1 means intervention maintenance period) with 15, 3-month time periods, and an average of 420(= 30 × (15–1)), 11–12 year old subjects per practice with an average of 30 subjects per practice per 3-month (for a total sample size of 30 × (15–1) × 9 = 3,780 subjects) achieves 80% power to detect a minimum difference of 0.094 to 0.118 in initiation rate between the intervention maintenance period (depending on the initiation rate in the control period, see Table 4) and the control period using a two-sided Wald Z-Test, an ICC of 0.026, and a significance level of 0.050 (PASS version 2022). This study design achieves 80% power to detect a minimum difference of 0.039 to 0.112 in the HPV completion rate between intervention maintenance and control periods depending on the completion rate in the control period and the value of ICC of 0.003 (Table 4).

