#### Statistical analysis plan

The same analytic strategy will be applied to each age group (11–12 vs. 13–17) for each HPV outcome separately. Both patient level characteristics (e.g., gender and ethnicity) and practice level characteristics (e.g., practice location and size) will be summarized using descriptive statistics and compared across the three FQHC groups using ANOVA or Kruskal-Wallis test for continuous variables and Chi-square or Fisher’s exact test for categorical variables. To compare the effect of facilitator-driven implementation strategies during the exposure period with the control period on the binary HPV outcomes, generalized linear mixed models (GLMMs) will be used with fixed effects for time and intervention as well as a random effect for practice, while considering patient-level and practice-level characteristics as needed. Heterogeneity of intervention effects will be examined by testing the interaction terms between intervention and potential effect.

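### Initiation and completion are both primary at the full 0.05, one section labels only initiation as primary, and the text does not say whether one or both must succeed

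*Protocol article*

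**What the plan says.** Under Effectiveness outcomes, the primary outcome "is timely HPV vaccine initiation and completion (2 doses) rates of 11-12 year olds". The Data collection section of the implementation component repeats the pair: "We powered the trial based on the primary outcome of HPV vaccine initiation and completion of 11–12 year olds".

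Under Setting and randomization, the first inclusion criterion attaches the label to initiation and does not mention completion: "HPV vaccine initiation rate for 11–12 year old adolescents overall at their practice sites (primary outcome".

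Under Sample size justification, the design "achieves 80% power to detect a minimum difference of 0.094 to 0.118 in initiation rate", with "a two-sided Wald Z-Test, an ICC of 0.026, and a significance level of 0.050". The next sentence claims 80% power for completion, for differences of 0.039 to 0.112, from the same design and without restating an alpha. Table 4 has separate rows for the two rates, with ICCs of 0.026 and 0.003.

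The Statistical analysis plan section says: "The same analytic strategy will be applied to each age group (11–12 vs. 13–17) for each HPV outcome separately". The article states no testing order, no division of alpha and no rule on whether one or both rates must be significant.

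**The concern.** The primary outcome is written in the singular but contains two rates. They are not a composite, because they have different ICCs, control rates and detectable differences, and each gets its own model. The trial's overall false-positive rate and its overall power depend on how the two results are combined, and the article leaves that open while publishing an error rate and a power for each.

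At stake is what the trial may conclude when the two disagree. A split result is plausible. Completion needs a second dose 6 to 12 months after the first, and the FQHCs' 2019–2021 completion rates (below 1% to 14.7%) are far under their initiation rates (24.6% to 40.9%). At a 3% control rate, Table 4 needs completion to reach 6.9%, more than double, for 80% power. If initiation rose and completion did not, the text would not say whether the primary objective had been met.

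**Working it through.** **Inputs.** From Sample size justification and Table 4: 9 practices in 3 FQHCs, 15 three-month periods of which 14 are counted per practice, 30 patients per practice-period, ICC 0.026 (initiation) and 0.003 (completion), 80% power, two-sided 0.05 stated for initiation. Not given: the layout in Table 3 (figure not shown) and the correlation ρ between the two test statistics. Both are assumptions below.

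**Step 1: reproduce Table 4.** Stepped-wedge linear model with fixed period effects and a practice random intercept, total variance p(1−p) at the control rate p, between-practice variance ICC × p(1−p). Detectable difference = (1.960 + 0.842) × SE = 2.802 × SE. With one transition period and crossovers two periods apart, all 12 rows reproduce, with power between 79.7% and 80.3%. Examples:
- Initiation, p = 0.5: SE 0.0421, so 2.802 × 0.0421 = 0.118 (Table 4: 0.118).
- Completion, p = 0.10: SE 0.0246, so 2.802 × 0.0246 = 0.069 (Table 4: 0.069).

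**Step 2: which alpha was used for completion?** Solving each row for alpha at 80% power gives 0.049 to 0.051 for both outcomes. A check on Table 4's own figures agrees. Detectable difference divided by √(p(1−p)) is about 0.236 for initiation (0.118/0.500) and about 0.229 for completion (0.092/0.400 = 0.230; 0.112/0.490 = 0.229). Planning completion at 0.025 would multiply its figure by 1.10, to about 0.252, which Table 4 does not show. So the full 0.05 was used for both.

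**Step 3: either rate suffices.** If the tests are independent, the family-wise error is 1 − (1 − 0.05)² = 0.0975. The upper bound under any dependence is 0.05 + 0.05 = 0.10. With positive correlation (bivariate normal, ρ assumed):

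| ρ | 0 | 0.2 | 0.4 | 0.6 | 0.8 | 0.9 | 1.0 |
|---|---|---|---|---|---|---|---|
| Family-wise error | 9.75% | 9.6% | 9.3% | 8.7% | 7.8% | 7.0% | 5.0% |

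**Step 4: both rates required.** The error is at most 5%. Joint power when both true differences equal their Table 4 values: 0.80 × 0.80 = 64% at ρ = 0, 70% at ρ = 0.6, 73% at ρ = 0.8.

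**Step 5: initiation alone is primary.** The 5% error and 80% power for initiation stand as printed, but Data collection and Effectiveness outcomes then misstate the primary outcome.

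The results in Steps 3 and 4 do not depend on the layout inferred in Step 1.

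**The case against.** The strongest reply is that this is a condensed article and a multiplicity rule normally sits in the analysis plan, which is not shown. As far as a missing procedure goes, that is right, and a missing procedure alone would not be a finding. What remains is in the article itself: the primary outcome is labelled in two ways, and power is published for both rates at the full 0.05. An analysis plan that split alpha equally would conflict with Table 4, since at 0.025 each the power at the printed differences falls to about 71%.

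Second, no alpha is written for completion. That is correct; 0.05 is inferred from Table 4, and a planning alpha is not a stated decision rule.

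Third, a reader might infer that the trial has two independent routes to success and a false-positive rate of about 10%. The documents do not support that. Nothing says either rate is enough, and the singular noun joined by an and fits a both-required reading at least as well. Nor are the routes independent: every completer is an initiator in the same practices, so positive correlation is likely and 9.75% probably overstates the error even if either suffices.

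Fourth, a reader might call a split result the likely outcome. The dose interval and low baseline completion make it plausible, but no figure makes it likely: the comparison uses the maintenance period after a transition, and at control rates of 3% to 15% the detectable differences for completion (0.039 to 0.082) are smaller than any for initiation.

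Fifth, the eligibility criterion does not say that initiation alone is primary. That is also fair. The parenthesis conflicts with the other sections but is thin support for choosing between them.

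**Conclusion.** The point holds as a conflict between sections and an incompletely fixed error and power statement. It does not establish that the trial's false-positive rate is 10%. With two primary rates and no order, the printed 5% and 80% cannot both describe the primary conclusion. If either rate suffices, the error is above 5% unless the tests are perfectly correlated: at most 10%, 9.75% under independence, 9.3% to 7.8% for ρ from 0.4 to 0.8. If both are required, the error is controlled but joint power is about 64% to 73% for ρ from 0 to 0.8. These figures rest on alpha 0.05 for each rate (stated for initiation, implied for completion), approximate normality of the test statistics, an assumed ρ, and, for power, true differences equal to those in Table 4. The sponsor should correct this; the change is small.

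**What to change.** Reconcile Setting and randomization, Data collection and Effectiveness outcomes with one rule. Initiation at 11–12 years is tested first at two-sided 0.05; completion at 11–12 years is tested at two-sided 0.05 only if initiation is significant; the 13–17 outcomes stay secondary, without confirmatory claims. This holds the family-wise error for the two 11–12 rates at 5% for any correlation, and it fits the label in the eligibility criterion.

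The edit is about one sentence in each section. Sample size and Table 4's alpha do not change. There are two costs. No confirmatory claim on completion is possible if initiation fails. The 80% for completion also becomes conditional on initiation passing: under independence it is 0.64/0.80 = 80%, and higher with positive correlation, but the unconditional chance of a completion claim is the joint 64% to 73%. The power section should say so.

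Other valid choices exist. Requiring both rates needs the joint power stated. An equal split at 0.025 each keeps the error at or below 5%, but power at the printed differences falls to about 71%, or the detectable differences grow by a factor of 1.10 (initiation 0.104 to 0.130, completion 0.043 to 0.124). The fixed sequence is the one that leaves Table 4 unchanged.

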### Recruitment, sample size, and retention plan

In Year 1, the academic research team and FQHC leadership will engage with practice sites to introduce practice coordinators, HCP, and staff to the study and establish a memorandum of understanding (MOU) outlining what study participation involves. Once FQHC leadership sign the MOU, we will randomize the FQHC. Participating HCP (*n* = 36; 4 per practice), staff members (*n* = 45; 5 per practice), implementation team (*n* = 36; 4 members per practice), and parents of patients aged 11–17 (*n* = 225; 25 per practice). HCP (*n* = 36; 4 per practice) and staff identified to serve as Immunization Navigators will receive the training and education. We will also conduct semi-structured interviews with the implementation team from each practice setting (*n* = 36) to identify key factors that influence sustainability of the strategies twelve months after implementation. We will only collect electronic health record (EHR) data from a sample of patients aged 11–12 and 13–17 based [73]. Our outcome data will be single measurements taken from individual patients, but we will randomly select patient EHR data for each data pull (cross-sectional data). See Fig. 2 for participant timeline.

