#### Measurement and evaluation

We will assess primary and secondary effectiveness outcomes during the control period and after every 3 months, using de-identified, randomly selected, EHR data from patients aged 11–12 and 13–17 per practice. We will incorporate the general guidelines of the Immunization Quality Improvement for Providers protocol developed by the CDC [73]. The protocol recommends collecting 50 EHRs for every 150 patients. A trained information technology specialist, who is employed at each site (PVHC, CHN, and SBCHC), will provide de-identified, randomly selected, EHR data to the data manager. The external facilitator will be responsible for evaluation activities related to HCP, immunization navigators, and practice staff. Immunization navigators will enter and store process evaluation data onto REDCap. We will use these data to evaluate the clinical practice plan and track immunization uptake and dose compliance through the EHR. Implementation outcomes will be assessed using pre-post surveys in the baseline assessment and EHR reports. We will use observational data in the form of monthly meeting notes and external facilitator debriefs to assess the complexity associated with *context* and the *recipients* involved in the implementation at the practice settings as they influence implementation.

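### As written, the completion rule follows the patient's age band, so a two-dose history that is complete at 11–14 scores as incomplete when sampled at 15–17

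*Protocol article*

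**What the plan says.** The Effectiveness outcomes section gives three completion rules, each attached to an age band.

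- Ages 11–12 (primary): the outcome is "timely HPV vaccine initiation and completion (2 doses) rates of 11-12 year olds", and "We define completion as a second valid dose 6–12 months after their first dose".
- Ages 13–14 (secondary): "For 13-14 year olds, we define completion as valid dose 6–12 months after their first dose".
- Ages 15–17 (secondary): "For 15–17 year olds, we define completion as a second valid dose 1-2 months after their first dose and a third valid dose", the third dose being placed at 6 months from the first.

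The last two bands form one secondary outcome, "completion (2 or 3 doses) for adolescent patients 13-17 years old (catch-up". The Statistical analysis plan section analyses 11–12 and 13–17 as the two age groups, so two different rules operate inside the 13–17 analysis.

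Age otherwise appears only as the age of the patient whose record is drawn. The Recruitment, sample size, and retention plan section says "We will only collect electronic health record (EHR) data from a sample of patients aged 11–12 and 13–17" and "we will randomly select patient EHR data for each data pull (cross-sectional data". The Measurement and evaluation section likewise refers to "randomly selected, EHR data from patients aged 11–12 and 13–17 per practice". The article nowhere makes the rule depend on age at first dose, and nowhere says how a series finished in a younger band is to be counted later.

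**The concern.** Completion of a vaccine series is a property of the dose history. Once a history meets the criterion, growing older should not undo it. Under these definitions it does. A record with two doses at the 11–14 spacing has no dose at 1–2 months and no third dose, so it fails the 15–17 rule although nothing in it has changed.

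What is at stake is the secondary completion outcome for ages 13–17. Three of its five years of age fall under the 15–17 rule. In those years, anyone whose completion rests on a two-dose series begun by 14 is recorded as a failure. The reported rate then mixes true non-completion with completion under a rule that the article itself accepts at younger ages.

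**Working it through.** **Step 1. Apply the three rules to one dose history.** Take a first dose at age 11 and a second valid dose 8 months later, with nothing after that.

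| Age when the record is sampled | Rule applied | Result |
|---|---|---|
| 11–12 (after the second dose) | two doses, 6–12 months apart | complete |
| 13–14 | two doses, 6–12 months apart | complete |
| 15–17 | second at 1–2 months, third at 6 months | not complete |

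This needs no assumption and no outside guideline.

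**Step 2. A boundary case.** Take a first dose at 14.5 years and a second at 15.1 years. The gap is 0.6 × 12 = 7.2 months, inside the 6–12 month window. Sampled at 14, the record shows one dose. Sampled from 15 on, it meets the three-dose rule's requirements neither in timing nor in number. It is complete at no pull.

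**Step 3. Effect on the 13–17 rate.** The article gives no clinic completion rate for 13–17 and no ages at first dose, so this step rests on assumptions:

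- the five years of age 13 to 17 have equal shares in the sample, giving 2/5 at 13–14 and 3/5 at 15–17;
- true completion is the same at each age;
- s is the share of 15–17 year old completers whose completion is a two-dose series started by 14.

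Then measured/true = 2/5 + (3/5)(1 − s).

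- s = 0.25: 0.40 + 0.60 × 0.75 = 0.85
- s = 0.5: 0.40 + 0.60 × 0.50 = 0.70
- s = 1: 0.40 + 0.60 × 0 = 0.40

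For a purely illustrative true rate of 30%, the recorded rates are 25.5%, 21% and 12%.

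**Step 4. Can series completed during the trial be affected?** The design has 15 three-month periods, so the first and last are 14 × 3 = 42 months apart. Ages 11–14 span 48 months. If ages are uniform (assumption), 42/48 = 87.5% of those aged 11–14 in the first period are 15 or older by the last. Series completed under the two-dose rule during the trial can therefore reach the band that does not recognise them.

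**Step 5. What is not affected.** The stated sample size concerns 11–12 year olds and reproduces exactly: 30 × 14 = 420 per practice, and 420 × 9 = 3,780. The Table 4 differences were also reproduced to within 0.002, using a standard stepped-wedge variance formula and a crossover pattern chosen to fit, because Table 3 is not shown. Both use only the 11–12 age group, where a single completion rule applies.

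**The case against.** The strongest reply is that age at first dose was meant. The 13–17 outcome is labelled catch-up and allows two or three doses, which suits late starters, and the 15–17 sentence could describe those who begin at 15–17. A journal article also condenses, and the CDC measurement protocol that it cites may settle the point. This reading is possible, but the article never states it, and every other use of age refers to the patient sampled. Nor does limiting the outcome to late starters help: a two-dose series begun at 13 and finished within the year still fails at 15. This is also not an omission, because the three rules are written out and give conflicting answers for one history.

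Other parts of the reply do stand, and they rule out stronger readings.

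- A reader might infer that individual children will be seen to flip from success to failure. The data are de-identified, single measurements from fresh random samples, so no child is followed. The point concerns how a given dose history is scored.
- A reader might infer a demonstrated bias against the later quarters, where more practices are exposed. The planned model has fixed time effects, which largely absorb ageing common to all practices. What could remain is extra two-dose completion before 15 caused by the strategies, in patients later sampled at 15–17, to a degree that depends on how long the practice has been exposed. That would pull the contrast toward the null, but nothing in the article allows it to be sized.
- A reader might take the 45% statewide completion figure in the Introduction and conclude that it would be recorded as 0.40 × 45% = 18%. That requires s = 1, so that no completer aged 15–17 started at 15 or later. The article gives no support for that extreme, and 45% is not a rate for these clinics.

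**Conclusion.** Wrong as written. The age-band definitions, applied to records sampled by patient age, score the same dose history as complete at 11–14 and incomplete at 15–17. This understates the secondary 13–17 completion rate whenever some 15–17 year old completers finished a two-dose series started by 14.

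The understatement is 15%, 30% or 60% of the true rate for s = 0.25, 0.5 or 1, given equal age shares and equal true completion by age. The value of s is unknown, and s = 1 is only the upper bound on the loss. These figures describe the level of the rate, not the intervention effect. Attenuation of the effect is possible but not shown. The point is confined to this one secondary outcome. Initiation at 13–17, the primary outcome for 11–12 year olds, the sample size and Table 4 stand as they are.

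**What to change.** Reconcile the definitions in the Effectiveness outcomes section. For each sampled record, select the completion rule by age at first dose rather than age at the pull. State that a dose history meeting the rule for its starting age counts as complete whatever the age at sampling. This is a rule per record and needs no linkage of patients across pulls. The number of doses and the intervals for each starting age remain the sponsor's decision.

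The cost is one sentence in the outcome definition and one derived variable. The interval rules already require dose dates, so age at first dose can be derived provided that the extract carries date of birth or age at each dose.
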